### Recruitment

Once eligibility criteria have been checked, patients from French comprehensive cancer care centers or hospitals will be invited to join the study.

Before inclusion, patients should read and understand the study information letter and then should date and sign the informed consent form (ICF) to allow them to join the study.

The coordinating center will be notified of each inclusion before completion of the first QoL questionnaire (inclusion document will be completed and returned to Paul Papin Center, Angers by fax).

Since eligibility criteria will be checked and patients' ICF will be collected, the first QoL questionnaires and the test-retest (3 days after the first completion) will be completed (before randomization) in the following order: QLQ-C15 PAL, MVQOLI, and QUAL-E.

After completion of the retest QoL questionnaire, the eligibility criteria and date of signed informed consent will be collected on a dedicated internet site to allow e-randomization with a personal log-in and password (Tenalea software). The study coordinator will then be able to randomize patients. The allocated arm will be sent to investigators, to the methodologists, the principal investigator and the coordinating center by email.

Patients will be randomized after the test-retest to limit the number of non-assessable patients for reproducibility.

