### Sample size

#### Primary endpoint

To study the validity of the questionnaires, the selected primary outcome is reproducibility assessed by intraclass correlation coefficients (ICC).

Taking into account the number of dimensions for each QoL questionnaire as well as the number of scores (continuous variable) for which the ICC will be calculated, using an unilateral alpha type one error of 0.001, a power of 80% and the following hypotheses (N'Query:Advisor V7):

H0: an ICC < 0.5 is uninteresting

H1: an ICC ≥ 0.65 is the minimum required for reproducibility

It will be necessary to include 338 patients.

Taking into account that 10% of patients will be lost to follow-up, it will be necessary to include 372 patients.

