#### Primary objective analyses

This study will respect the FDA psychometric validation methods [7].

The first objective is to validate translation of QUAL-E and MVQOLI by checking the psychometric properties.

1. Validity [32-34]: Face validity and content validity: The translated questionnaires will be analyzed by patients and experts to check that the items of the questionnaires are in line with to the original version (major domains treated, question ambiguity). This step was conducted by the '*Qualité de vie et cancer' *platform experts group during cross-cultural translation of the English questionnaires.

Criterion validity: We will check that the translated tools correlate with reference QoL or clinical criteria by calculating correlation coefficients. QLQ-C15 PAL will be treated as the gold standard for QoL tools. A strong correlation between the measures given by the questionnaires and those given by the QLQ-C15 PAL will constitute proof of criterion validity. We will also use the WHO performance status and the performance palliative scale (PPS). These variables will be also dichotomized to calculate the sensitivity and specificity of QoL tools using ROC curves.

Construct validity: This psychometric property will be checked by calculating establishing convergences and differences with the other variables. Factorial analyses as well as Item Response theory methods will be used.

2. Reliability [32-34]: Effect size and the standardized response mean will be computed between each follow-up and then analyzed according to Cohen's classification.

Sensitivity to change:

Internal consistency: we will estimate the strength of the inter-correlations between items, and validate underlying dimensions. We will calculate Cronbach's alpha as an estimator of this internal consistency for each dimension of the QoL questionnaires (at each time assessment). This estimator must be greater than 0.7 to consider a domain homogeneous, but not too close to 1, which would mean that some questions are redundant.

Reproducibility will be studied by calculating ICC using analysis of variance for repeated measurement. An ICC of 0.65 is the minimum required for reproducibility. A Bland and Altman graph will be also done [35,36].

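### The 338 patients for the primary endpoint match a two-sided, not the stated one-sided, alpha of 0.001, and the analysis criterion of ICC 0.65 is not reconciled with the sized test against 0.5

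*Protocol article*

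**What the plan says.** In the protocol article, Sample size (Primary endpoint), "the selected primary outcome is reproducibility assessed by intraclass correlation coefficients (ICC"). The hypotheses are "H0: an ICC < 0.5 is uninteresting" and "H1: an ICC ≥ 0.65 is the minimum required for reproducibility". The error rates are set "using an unilateral alpha type one error of 0.001, a power of 80" per cent. The strict alpha is explained by the number of dimensions and scores to be tested. The result is "It will be necessary to include 338 patients", and then "Taking into account that 10% of patients will be lost to follow-up, it will be necessary to include 372 patients".

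Each patient gives two measurements, since under Recruitment "the first QoL questionnaires and the test-retest (3 days after the first completion) will be completed (before randomization").

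In Primary objective analyses, the reproducibility paragraph says that the ICC will be computed by repeated-measures analysis of variance, and adds: "An ICC of 0.65 is the minimum required for reproducibility". That paragraph mentions no test against 0.5, no confidence limit and no alpha.

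**The concern.** Two things do not fit together.

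First, alpha, sidedness, power and N in the sample-size section should describe one test. If 338 cannot be reached from the other inputs, a reader cannot tell which test is planned, and whoever writes the analysis plan must guess whether to use a one-sided or a two-sided 0.001.

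Second, a study sized to reject 0.5 declares success once the estimate is far enough above 0.5, which at this sample size happens below 0.65. The analysis section names only 0.65. An observed ICC of, say, 0.63 would reject 0.5 at the planned alpha and yet could be reported as falling short of the minimum. For the primary endpoint, the same result could then be called a success under one section and a failure under the other. The Discussion says that failed validation may lead to the construction of a new questionnaire, so the verdict has consequences.

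**Working it through.** **Inputs.** Null ICC 0.50, alternative 0.65, alpha 0.001 one-sided, power 80%, N 338 and 372, loss 10% (all from Sample size, Primary endpoint); two measurements per patient (Recruitment).

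**Step 1: reproduce 338.** With two measurements, the Fisher z formula is n = ((z_alpha + z_power) / (atanh 0.65 − atanh 0.50))² + 3.
- atanh 0.65 − atanh 0.50 = 0.7753 − 0.5493 = 0.2260; z_power = 0.8416.
- One-sided 0.001, z_alpha = 3.0902: (3.9319 / 0.2260)² + 3 = 305.7, so 306.
- Two-sided 0.001, z_alpha = 3.2905: (4.1321 / 0.2260)² + 3 = 337.3, so 338.

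The stated figure is matched exactly by the two-sided alpha with every other input unchanged. Two other methods agree. The Walter–Eliasziw–Donner approximation gives 304 one-sided and 336 two-sided. The exact F distribution of the ANOVA ICC gives 305 to 306 one-sided and 337 to 338 two-sided. Across methods the stated inputs need 304 to 306, about 9.5% fewer than 338.

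**Step 2: what 338 delivers for the test against 0.5 when the true ICC is 0.65 (exact F).**

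| Test of ICC 0.5 at n = 338 | Power | Smallest observed ICC that rejects 0.5 |
|---|---|---|
| One-sided 0.001 (as stated) | 85% | about 0.616 |
| Two-sided 0.001 | 80% | about 0.622 |

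**Step 3: the allowance for loss.** 338 × 1.1 = 371.8, which is the stated 372. But 372 × 0.9 = 334.8, so about 334 evaluable patients remain. To keep 338 after a 10% loss, 338 / 0.9 = 375.6, so 376. The gap is 4 patients (1.1%). At 334, power is about 85% one-sided and 79.5% two-sided.

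**Step 4: the 0.65 criterion if applied to the observed ICC.** The probability that the observed ICC is at least 0.65, from the exact F distribution at n = 338:

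| True ICC | Probability of passing |
|---|---|
| 0.50 | 0.00002 |
| 0.60 | 6.6% |
| 0.65 | 50.0% |
| 0.676 | 80% |
| 0.70 | 95% |

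The 50% at a true ICC of 0.65 does not depend on N: it is 50.0% at 306, 338 and 372. Under this rule neither the 80% power at 0.65 nor the 0.001 error rate at 0.50 applies.

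**The case against.** The strongest reply concerns the 0.65 sentence. It nearly repeats the wording of H1 in the sample-size section, so it may only recall the planning alternative. In the same section the criterion for Cronbach's alpha is tied expressly to the estimator, while the ICC sentence is not. A statistical analysis plan is promised before database lock and may fix the rule. This stands in part: the text does not say that the observed ICC must reach 0.65. A reader might infer that the primary endpoint has 50% rather than 80% power. The protocol does not support that as a flat statement, because it needs both the cut-off reading and a true ICC of exactly 0.65; at a true ICC of 0.70 the same rule passes 95% of the time. What remains is that the protocol names a threshold of its own and does not connect it to the test it was sized for. That is more than a detail left to a later plan.

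On 338, the reply is that changing one label explains it and that the discrepancy is conservative. Both are correct. A reader might infer that the number is inexplicable or the study too small; neither holds, since the one-sided test needs only about 306. On 372, the reply that four patients do not matter is also fair.

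A reader might further multiply the 80% across all domains to get a very low chance that every one passes. The protocol states no rule that all must pass, and domains answered by the same patients need not be independent, so such a figure has no basis here.

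**Conclusion.** The sizing of the primary endpoint is wrong as written: one-sided 0.001, 80% power and 338 patients do not describe the same test. The stated inputs need about 306, and 338 belongs to a two-sided 0.001. The error is conservative (about 85% power one-sided at 338) and leaves no shortage of patients. The 372 is a minor slip that leaves about 334 evaluable.

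The 0.65 criterion and the sized test against 0.5 are not reconciled. Whether this costs power depends on what 0.65 applies to, which the protocol leaves open. As a cut-off on the estimate it gives 50% at a true ICC of exactly 0.65 and 80% at about 0.676. As a restatement of H1 it costs nothing, but then the analysis section gives no decision rule.

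These figures assume two measurements per patient and the usual ANOVA model for the ICC, and they apply to one score at a time.

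**What to change.** 1. **Sample size, Primary endpoint.** Either change the alpha from unilateral to bilateral and keep 338 with 80% power, or keep it unilateral and restate the power at 338 as about 85%.
2. **Same section.** State that 372 leaves about 334 evaluable after 10% loss (79.5% power two-sided, about 85% one-sided), and that 376 would be needed to keep 338.
3. **Primary objective analyses.** State one decision rule, the same in both sections:
   - the lower confidence limit of the ICC at the planned alpha exceeds 0.50, noting that at 338 patients this corresponds to an observed ICC of about 0.616 (one-sided) or 0.622 (two-sided); or
   - the observed ICC is at least 0.65, with power restated as 80% at a true ICC of about 0.676 and 50% at 0.65.

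   The first keeps the test that was sized but accepts estimates below 0.65; the second keeps 0.65 as a minimum on the estimate. The choice is the sponsor's, and it should be made before the reproducibility data are examined. Trial status reports 12 of 372 patients included at submission.

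The cost is wording and restated figures. No extra patients are required.

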#### Secondary objectives

1. To longitudinally assess QoL of cancer patients until death using QLQ-C15 PAL, the French version of QUAL-E, and of Missoula Vitas Quality of Life Index (MVQOLI) Statistical analyses will be conducted to investigate longitudinal changes of each QoL dimension: description of missing QoL scores; missing QoL questionnaires and scores will be studied and classified according to Diggle and Rubins' method to determine whether the missing data were random or not: Missing Completely At Random, Missing At Random, Missing Not At Random [30,31,37,38].

Univariate and multivariate Logistic regression will be done to construct a clinical model to predict missing QoL and to investigate the random nature of missing QoL data. The numbers of missing scores will be described according to the patient subgroups and compared using ANOVA and Mixed Anova for repeated measurement.

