## Background

The end of life for cancer patients is the ultimate stage of the disease. However, in this setting, improving quality of life (QoL) and the wellbeing of patients should remain a major concern. Given the profoundly personal concerns involved, patients' perceptions of the end of life are difficult to assess and have therefore been insufficiently studied. Clinicians, nurses, and other paramedical personnel are required to provide individualized care adapted to the end of life in order to improve patients' QoL and wellbeing [1,2].

Today, there is no consensus to define the time frame related to the 'end of life' of a cancer patient [3]. For example, depending on the cancer site, the 'palliative' period could vary from a few days to a few months. Moreover, the palliative and 'end-of-life' periods could overlap, but the therapeutic goals for these two periods should not be the same. In order to provide optimal care, it seems crucial to distinguish between these two periods as the former has a more therapeutic goal while the latter is to accompany patients as they near death. This ultimate stage of disease could require caregivers to meet new demands not only from patients, but also from their relatives.

To our knowledge (Patient Reported Outcome and Quality Of Life Instruments Database) [4-6] there are no French validated tools to assess health-related QoL for cancer patients at the end of life. QoL is a major endpoint to assess therapeutic strategies in cancer patients, particularly in a palliative setting when no benefits in overall survival can be expected. In this context, QoL should be considered the primary endpoint for trials [7,8].

QoL at the end of life could be evaluated using generic QoL questionnaires like EORTC QLQ-C30 and/or the Medical Outcome study Short Form 36 (SF-36) or by using questionnaires focusing on symptoms. For example, the Edmonton Symptoms Assessment System (ESAS) is a dedicated tool to assess pain [9]. Other tools allow caregivers to assess depression [10] or fatigue [11].

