### Population

To be eligible, patients should have been diagnosed with advanced cancer (with any cancer site) and treated or not with palliative intent (chemotherapy, analgesic radiotherapy, surgery without curative intent), with an ECOG or a WHO performance status ≥ 2, a life expectancy ≥ 1 month, and an age ≥ 18 years.

Patients should have been informed about the palliative stage of the disease and should have been followed for at least 1 month by a palliative caregiver to be included in the study.

The non-eligibility criteria are: a psychiatric disease that compromises understanding of the study objectives and/or informed consent and/or the inability of patients to follow the study design for psychological, social, family, or geographical reasons.

Written informed consent is required before inclusion.

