### Completion of QoL questionnaire

The QoL questionnaires will be completed before randomization and then every month until death in a time driven design fashion.

Using test-retest methodology, the QLQ-C15 PAL, MVQOLI, and QUAL-E questionnaires will be completed 3 days after the first completion at baseline and before randomization [27].

Though a maximum delay of 15 days is usually allowed between completions to check reproducibility, since these patients have a specific end-of-life profile with sometimes a rapid deterioration in general health status, a maximum delay of 3 days was chosen to minimize the 'risk' of changes in health status.

Since the QUAL-E questionnaire should be completed using a direct interview; patients should complete it last to prevent social desirability bias on QLQ-C15 PAL and MVQOLI evaluations [27].

In order to prevent missing QoL data [28], if a patient is unable to complete questionnaires due to poor health status, QLQ-C15 PAL and MVQOLI could be completed with the help of a proxy (from the medical team) who will have to record the patient's answers without interpretation [29]. A specific item will be completed to take this information into account for the longitudinal analysis of QoL.

All patients will complete QoL questionnaires every month until death.

In arms C and D, depending on patients' health status or perceived QoL, patients will be free to complete the QLQ-C15 PAL and MVQOLI questionnaires (spontaneous QoL completion in an event drive design) between two planned evaluations. A patient CRF including QLQ-C15 PAL and MVQOLI questionnaires, the date of completion, the perception of QoL changes using the Jaescke transition question [30]), and a space for free comments will be created. This booklet will be given to the patients after randomization.

The QoL questionnaires will be administered in a homogeneous way by the same person, a nurse specialized in palliative care, a psychologist, or if necessary a clinical research assistant (CRA), throughout the patient follow-up until death.

Completed questionnaires should be returned to one of the CRAs assigned to the study. In order to deal with holidays, a minimum of two full-time CRAs will be required and identified for each participating center (Table 2).

**Table 2 T2:** Center's participation agreement

Organization	City
Cancer care center Paul Papin	Angers, France

Cancer care center Léon Bérard	Lyon, France

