### Statistical analyses

A statistical analysis plan will be written before the database is locked.

The population and clinical characteristics will be described (sex, age, family situation, cancer site).

The rate of QoL completion will be described for each questionnaire at each follow-up. QoL scores will be described at each follow-up.

Continuous variables will be described by means (standard deviation) and median (minimum-maximum). Qualitative variables will be described by frequencies and percentages.

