### Longitudinal analyses

QoL will be described at each follow-up and then longitudinally analyzed using a mixed model analysis of variance for repeated measurements to investigate and test a time trend for QoL [39-41]:

These models will have to take into account non-random missing data.

With simple imputation methods for sensitivity analyses:

Mean QoL score imputation: Means will be calculated for the whole population and for specific patient profiles (cancer location, age, sex, and so on) at each follow-up and then will be imputed for patients with missing QoL scores

Extreme QoL score imputation. This method could be used when the missing data are due to a pejorative event such as death or disease progression.

With 'pattern mixture' models [42,43]:

Qualitative variables will be created to describe missing QoL score profiles and to define patterns for these analyses (no missing score, intermittent and drop-out profiles).

Time until definitive QoL score deterioration:

Analyses of time until a definitive QoL score deterioration (TUDD) will be estimated using the Kaplan-Meier method [44].

The TUDD of a score will be defined as the time interval between randomization and the first decrease in the MCID score ≥ 5 points compared to the QoL score at inclusion with no further improvement in QoL score ≥ 5 points or in the case of patient who dropped out after a ≥ 5-point decrease, resulting in missing data.

Patients will be censored at the last QoL follow-up when no ≥ 5-point deterioration in the QoL score from baseline will be observed or for patients with a ≥ 5-point deterioration, but with a subsequent ≥ 5-point improvement as compared to baseline QoL score.

Patients with no available QoL scores will be included in the TUDD analysis, but censored immediately.

2. To assess the impact of therapeutic strategies on QoL at the end of life Since treatments and care strategies will be longitudinally collected, for exploratory purposes only, we will compare longitudinal QoL according to these strategies using mixed model analysis of variance and Log Rank tests and Cox models for the time to definitive QoL deterioration analyses.

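### Missing scores are compared between subgroups as raw counts although the number of forms due depends on survival, so the comparison can mislead where subgroups differ in prognosis

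*Protocol article*

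**What the plan says.** In the protocol article, under Secondary objectives, item 1, missing QoL data are to be described and classified by mechanism. Two analyses follow. The first is a regression: "Univariate and multivariate Logistic regression will be done to construct a clinical model to predict missing QoL", also meant to examine whether the data are missing at random. The second is the comparison at issue: "The numbers of missing scores will be described according to the patient subgroups and compared using ANOVA and Mixed Anova for repeated measurement".

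Four other places bear on it:

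- **Completion of QoL questionnaire** sets the schedule: "All patients will complete QoL questionnaires every month until death". There is no common end of follow-up.
- **Background** says that "depending on the cancer site, the 'palliative' period could vary from a few days to a few months". **Population** sets only a floor at entry, "a life expectancy ≥ 1 month".
- **Statistical analyses** plans a description with an implied denominator: "The rate of QoL completion will be described for each questionnaire at each follow-up". It is not broken down by subgroup, and the section does not say who counts as at risk at each follow-up.
- **Longitudinal analyses** says of extreme-score imputation: "This method could be used when the missing data are due to a pejorative event such as death or disease progression". Death thus appears as a cause of missing data, and the article does not say whether assessments after death count as missing.

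**The concern.** A patient can fail to return only a form that fell due. With monthly forms until death, a patient who lives eight months can miss eight, and one who dies in the third month can miss two. A count per patient is therefore roughly the product of two things: how many forms were due, and what share of them was missed. Only the second is missingness.

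If two subgroups differ in prognosis, the ANOVA of counts mixes the two. It can report a difference in missingness that is only a difference in survival. It can also fail to see that a sicker subgroup misses a larger share of fewer forms, which is the pattern an investigation of informative missingness most needs to find. If assessments after death are counted as missing, the distortion runs the other way and the shorter-lived subgroup appears to have more missing data.

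At stake is the subgroup comparison of missing data under secondary objective 1.

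**Working it through.** The documents give no figure for this comparison, so there is none to reproduce. They also give no survival estimate and no expected missing rate. What follows is an illustration under stated assumptions.

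**Inputs from the article.** Forms are monthly until death. The total is 372 (Sample size, Primary endpoint: "it will be necessary to include 372 patients"), split here into two subgroups of 372 / 2 = 186.

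**Assumptions.** Survival is exponential with median *m* = 2, 3 or 4 months. Forms are due at each whole month survived, up to month 12. Each due form is missing independently with probability *p* = 20%, 30% or 40%. The one-month life-expectancy criterion is not imposed as a minimum survival time.

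**Step 1: forms due.** The expected number due is the sum over k = 1 to 12 of 2^(−k/m), which equals q(1 − q^12)/(1 − q) with q = 2^(−1/m).

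- m = 2: 2.414 × (1 − 1/64) = 2.38
- m = 3: 3.847 × (1 − 1/16) = 3.61
- m = 4: 5.285 × (1 − 1/8) = 4.62

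**Step 2: expected missing count = p × forms due.**

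- Equal 30%, medians 2 and 4: 0.30 × 2.38 = 0.71 against 0.30 × 4.62 = 1.39. The count nearly doubles with no difference in missingness.
- 40% and 20%, medians 2 and 4: 0.40 × 2.38 = 0.95 against 0.20 × 4.62 = 0.92. A two-fold difference disappears, because the ratio of forms due (4.62 / 2.38 = 1.94) almost cancels it.

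**Step 3: simulated rejection rates.** There were 2,000 trials per row, tested at two-sided 5%. The proportion test compares total missing over total due while alive, with patient-level variance.

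| Median survival (months) | True missing per due form | Mean missing count | Count ANOVA rejects | Proportion test rejects |
|---|---|---|---|---|
| 3 v 3 | 30% v 30% | 1.08 v 1.08 | 4.2% | 6.0% |
| 2 v 4 | 30% v 30% | 0.71 v 1.38 | 99.95% | 5.2% |
| 3 v 4 | 30% v 30% | 1.08 v 1.39 | 52.8% | 5.8% |
| 2 v 4 | 40% v 20% | 0.95 v 0.93 | 5.6% | 100% |
| 3 v 3 | 40% v 20% | 1.44 v 0.72 | 99.8% | 100% |

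Rows 1 and 5 show that the count ANOVA works when survival is the same. Rows 2 to 4 show the failure when it is not.

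**Step 4: forms after death counted as missing, to month 12.** The expected count becomes 12 − (1 − p) × forms due. At equal 30%, medians 2 and 4 give 12 − 0.70 × 2.38 = 10.33 against 12 − 0.70 × 4.62 = 8.77 (simulated 10.34 and 8.76), and the ANOVA rejects in 100% of trials. Medians 3 and 4 give 67.3%. The direction has reversed.

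**The case against.** Five arguments count against the point.

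1. **A logistic regression is already planned.** The sentence just before the comparison plans one with missing QoL as the outcome, for the stated purpose of examining whether missingness is random. This stands as a real mitigation. It does not remove the problem: the count comparison is still planned beside it, the unit of the regression (form or patient) is not stated, and the two may disagree about the same subgroups.
2. **The mixed ANOVA may be per visit.** A total over follow-up is one value per patient and cannot be a repeated measure, so the mixed ANOVA probably uses the number of missing scores at each visit, which has a fixed maximum. Among patients still alive, that would largely remove the dependence on survival. This also stands in part. The sentence names a plain ANOVA as well, and a per-visit count is still confounded if the dead are counted as missing.
3. **The inputs are chosen.** Survival and missing rates are assumed, the subgroups are undefined in the article, and the 40% against 20% case sits close to exact cancellation. This is correct. The figures show direction and possible size, and are no forecast for this trial.
4. **Denominators belong in the SAP.** Often they do, and one is still to be written. Here, though, the article itself fixes the quantity, the contrast and the test.
5. **Nothing downstream depends on it.** A reader might infer that a wrong answer here would change how the longitudinal models treat missing data. The documents do not support that. Longitudinal analyses requires those models to allow for non-random missingness in any case, and names imputation sensitivity analyses and pattern-mixture models without making any of them conditional on this comparison.

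**Conclusion.** The point holds in a limited form and is minor. Taken literally, a patient-level ANOVA of missing counts confounds missingness with survival wherever subgroups differ in prognosis. The article itself says the palliative period varies with cancer site, so such subgroups are plausible. Under the assumed medians of 2 and 4 months, false rejection is near 100%, and power is about 6% for a true 40% against 20%. At 3 and 4 months, false rejection is about 53%.

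A reader might go further and conclude that the comparison mainly measures survival whatever the grouping. That is not supported: with equal survival the count ANOVA kept its level (4.2%) and had 99.8% power, and similar survival is what randomisation leads one to expect between arms.

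The harm is confined to the missing-data comparison under secondary objective 1. The ICC analysis, the sample size and the two randomised comparisons are untouched. The percentages rest on exponential survival, independent missingness within patients, equal subgroups and a 12-month horizon. The direction follows from the schedule alone once survival differs.

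**What to change.** Replace the ANOVA of numbers by a comparison of the proportion missing among scheduled assessments that fell due while the patient was alive. The simplest route is to extend the logistic regression already planned to one record per due form, with subgroup as a covariate and a GEE or random patient effect for repeated forms. A count model with log(number of forms due) as offset would also serve.

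State that assessments after death are not due and are not counted as missing, and use the same definition of at risk for the completion rate described under Statistical analyses.

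The cost is a few sentences in the SAP and a little analysis work. Completion dates and reasons for non-completion are already to be collected, and follow-up to death should supply the date needed to count forms due.
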